## Abstract

**Background:**

Optimal secondary prevention antithrombotic therapy for patients with antiphospholipid syndrome (APS)-associated ischemic stroke, transient ischemic attack, or other ischemic brain injury is undefined. The standard of care, warfarin or other vitamin K antagonists at standard or high intensity (international normalized ratio (INR) target range 2.0-3.0/3.0-4.0, respectively), has well-recognized limitations. Direct oral anticoagulants have several advantages over warfarin, and the potential role of high-dose direct oral anticoagulants vs high-intensity warfarin in this setting merits investigation.

**Objectives:**

The Rivaroxaban for Stroke patients with APS trial (RISAPS) seeks to determine whether high-dose rivaroxaban could represent a safe and effective alternative to high-intensity warfarin in adult patients with APS and previous ischemic stroke, transient ischemic attack, or other ischemic brain manifestations.

**Methods:**

This phase IIb prospective, randomized, controlled, noninferiority, open-label, proof-of-principle trial compares rivaroxaban 15 mg twice daily vs warfarin, target INR range 3.0-4.0. The sample size target is 40 participants. Triple antiphospholipid antibody-positive patients are excluded. The primary efficacy outcome is the rate of change in brain white matter hyperintensity volume on magnetic resonance imaging, a surrogate marker of presumed ischemic damage, between baseline and 24 months follow-up. Secondary outcomes include additional neuroradiological and clinical measures of efficacy and safety. Exploratory outcomes include high-dose rivaroxaban pharmacokinetic modeling.

**Conclusion:**

Should RISAPS demonstrate noninferior efficacy and safety of high-dose rivaroxaban in this APS subgroup, it could justify larger prospective randomized controlled trials.

## Introduction

1

### Background and rationale

1.1

Stroke is the second leading cause of death worldwide [1] and the most important cause of adult complex disability [2]. Thrombotic antiphospholipid syndrome (APS) is an acquired autoimmune thrombophilia characterized by venous, arterial, and/or microvascular thrombosis in conjunction with persistent antiphospholipid antibodies (aPL): lupus anticoagulant (LA), immunoglobulin (Ig)G and/or IgM anticardiolipin antibodies (aCL), and IgG and/or IgM anti-beta 2 glycoprotein I (aβ2GP1) antibodies. Among patients with systemic lupus erythematosus (SLE), concomitant thrombotic APS is present in 7% to 15% [3] and confers an adverse prognosis [4,5]. It is estimated that 13.5% (range, 6.8%-23.3%) of individuals with stroke or transient ischemic attack (TIA) have aPL [6]; below the age of 50, approximately 17% (range, 2%-56%) of strokes and 12% (range, 2%-45%) of TIAs are associated with aPL [7]. Ten percent of patients with APS will have a stroke or TIA over 10 years [8]. The spectrum of ischemic brain lesions in APS encompasses white matter hyperintensities (WMHs) of presumed vascular origin and infarcts (subcortical/cortical) [9]. WMHs are an established correlate of small vessel cerebrovascular damage and exhibit face validity, with a systematic review demonstrating their value for predicting increased risk of stroke (hazard ratio [HR]; 95% CI: 3.3; 2.6-4.4), dementia (1.9; 1.3-2.8); and death (2.0; 1.6-2.7) [10]. In patients with aPL, cognitive impairment is common (11%-60.5%) and is associated with WMHs, ischemic lesions, and cortical atrophy [11].

The current standard of care for patients with APS-associated ischemic stroke/TIA or other ischemic damage is anticoagulation with warfarin/other vitamin K antagonist (VKA), with or without an antiplatelet agent. However, owing to a lack of substantive data, optimal antithrombotic therapy in this subgroup of APS patients is uncertain [12]. European Alliance of Associations for Rheumatology (EULAR) guidance [13] gives a range of antithrombotic options for initial ischemic stroke in APS patients: VKA at target international normalized ratio (INR) range of 2.0-3.0 (standard intensity) or 3.0-4.0 (high intensity), taking into account the individual’s risk of bleeding and recurrent thrombosis (level of evidence 1b/grade of recommendation B; Oxford Centre for Evidence-Based Medicine standards). Treatment with standard-intensity VKA plus low-dose aspirin is also included as an option (level of evidence 4/grade of recommendation C).

Warfarin/VKA treatment has several limitations, including recurrent thrombosis, which can occur in APS patients despite therapeutic VKA anticoagulation, with an annualized rate of 4.3% in the prospective Euro-phospholipid cohort of 1000 APS patients [8]. The variable dose-response and narrow therapeutic index of warfarin, along with its numerous drug [14] and dietary interactions, often necessitate frequent anticoagulant monitoring and dose adjustment. In APS patients, INR instability may be exacerbated by increased sensitivity of some thromboplastins to LA and, notably, potential for discordant results with point-of-care INR testing [15]. Direct oral anticoagulants (DOACs) have several advantages over VKA: fixed dosing without need for routine anticoagulant monitoring and considerably fewer drug [16] and dietary interactions. Rivaroxaban [17], a factor (F)Xa inhibitor, along with other DOACs, has emerged as standard of care in general population, with indications including treatment and secondary prevention of a first venous thromboembolism (VTE) [18] and thromboembolism prevention in atrial fibrillation [19].

Current guidance [13,20,21], however, in accordance with recommendations issued by the European Medicines Agency [22] and adopted by regulatory agencies worldwide, cautions against use of DOACs in APS patients with arterial thrombosis and/or triple-aPL positivity (concurrent presence of the 3 criteria aPL: LA, IgG and/or IgM aCL, and aβ2GP1). Two meta-analyses of randomized controlled trials (RCTs) [23,24] in APS patients found a significantly higher risk of subsequent arterial thrombosis during treatment with DOACs compared with warfarin (odds ratios of 5.17 [95% CI, 1.57-17.04] and 5.43 [95% CI, 1.87-15.75] for the other study), although risk of subsequent VTE was not increased. Notably, all previous RCTs of DOACs in APS patients have used standard intensity [[25], [26], [27], [28]] or prophylactic dose [28] DOACs. Further clinical studies are recommended to define the role of DOACs in APS patients, including the use of high-dose DOAC in those with arterial thrombosis [20,21], recognizing the heterogeneity of APS and need for a tailored approach according to thrombotic and laboratory phenotype.

### Objectives

1.2

This proof-of-principle trial compares the use of high-dose rivaroxaban with high-intensity warfarin for secondary prevention of ischemic stroke or other ischemic brain manifestations in patients with APS. The main objective is to demonstrate noninferior efficacy and lack of major safety signals. Our hypothesis is that high-dose rivaroxaban could represent a safe and effective alternative to high-intensity warfarin in this patient group.

## Methods

2

### Trial design, participants, interventions, and outcomes

2.1

The Rivaroxaban for stroke patients with APS (RISAPS) trial is a phase IIb prospective, randomized, controlled, noninferiority, open-label, proof-of-principle trial in adult patients with APS and previous ischemic stroke, TIA, or other ischemic brain manifestations. Eligible patients from participating centers in UK, after providing fully informed written consent, were enrolled and randomized 1:1 to either high-dose rivaroxaban 15 mg twice daily or high-intensity warfarin, target INR 3.5 (range, 3.0-4.0), the latter being regarded as standard of care in this study. The primary outcome for comparison of relative efficacy is the rate of change in brain WMH volume on magnetic resonance imaging (MRI), a surrogate marker of ischemic damage, between baseline and 24 months follow-up between these 2 treatment arms.

The study design was amended from phase II/III to phase IIb following revision of sample size target from 140 to 40 participants (minimum). This was necessitated by adverse recruitment factors, including in relation to the COVID-19 pandemic and decision to exclude triple-aPL-positive patients.

The official title of the trial is: Rivaroxaban vs Warfarin for Stroke Patients With Antiphospholipid Syndrome, With or Without SLE (RISAPS): a Randomised, Controlled, Open-label, Phase IIb, Non-inferiority Proof of Principle Trial.

### Participant inclusion criteria

2.2

1.Confirmed to have persistent aPL, defined as positivity of one or two aPL, ie, LA, aCL, and/or aβ2GP1 antibodies (IgG and/or IgM) at >40 GPL (IgG phospholipid units) or MPL (IgM phospholipid units) units or >99th centile of normal, on 2 or more occasions at least 12 weeks apart.2.One or more of a) ischemic stroke; b) TIA with evidence of either acute or chronic ischemic injury on brain MRI—including diffusion-weighted imaging lesion(s), previous cortical or subcortical infarction(s), or WMHs—and diagnosed by a clinician with expertise in stroke; c) brain infarcts (territorial or subcortical) or WMHs of presumed vascular origin on brain MRI, with or without cognitive impairment; and an expert clinical opinion that anticoagulation is a reasonable treatment option (with aim of preventing ischemic brain injury).3.Body weight ≥ 50 kg and ≤135 kg.4.Adequate contraception (barrier or hormonal) in women, unless postmenopausal or sterilized.

There was no requirement for the participant’s diagnosis, as per inclusion criteria (1) and (2), to have been made within a certain timeframe prior to enrolment, ie, both *de novo* and established cases were considered. Furthermore, eligibility was not restricted according to the participant’s antithrombotic treatment (active/historical), if any, prerandomization.

### Selected participant exclusion criteria

2.3

•Age < 18 years•Triple positivity for aPL (defined as concurrent presence of LA, IgG and/or IgM aCL, and aβ2GP1 antibodies at >40 GPL or MPL units or >99th centile of normal∗)•∗patients previously triple-aPL positive and subsequently single- or double-aPL positive on at least 2 occasions over at least 6 months, including once within 1 month prior to randomization, were not excluded•Pregnant or lactating women•Women planning to become pregnant within the 24 month follow-up period•Severe renal impairment with creatinine clearance < 30 mL/min (Cockroft and Gault)•Liver function tests: alanine transaminase > 3 × upper limit of normal•Cirrhotic patients with Child-Pugh B or C•Thrombocytopenia (platelets <75 × 10^9^/L)

Full exclusion criteria, including contraindicated concomitant medications, are listed in the Supplementary File.

### Interventions

2.4

Participants were randomized in a 1:1 ratio to either high-dose rivaroxaban 15 mg twice daily (film-coated tablets to be taken orally with food) or high-intensity warfarin, target INR 3.5 (range, 3.0-4.0) for 24 months. Participants on warfarin require INR monitoring by an appropriate anticoagulation clinic in line with usual practice. Adherence to trial medication is assessed by completion of the Medication Adherence Rating Scale (MARS) at each follow-up visit. In addition, for participants on warfarin, INR documentation is reviewed.

The Supplementary File provides further information relating to interventions, including safety processes to mitigate bleeding risk and criteria for anticoagulation review ± modification during trial (including bleeding and thrombosis, weight change, and moderate/severe renal impairment).

### Outcomes

2.5

The primary outcome is the rate of change in WMH volume (assessed on MRI—a surrogate marker of ischemic damage).

Secondary outcome measures, encompassing neuroradiological and clinical parameters of efficacy and safety, health economics, anticoagulation intensity, and exploratory outcomes including rivaroxaban pharmacokinetic (PK) modeling, are outlined in the Table.

**Table tbl1:** Secondary outcomes of trial.

A. Efficacy
1. Neuroradiological markers i) Rates of change in mean diffusivity (assessed on MR imaging) ii) Rates of change in mean fractional anisotropy (as a measure of microstructural white matter damage derived from diffusion tensor imaging) iii) Rates of change on T1-weighted volumetric images of total brain volume iv) Rates of changes on T1-weighted volumetric images of white matter hyperintensities v) Rates of change on T1-weighted volumetric images of grey matter volume vi) Total number of brain infarcts per person as well as the number of these events overall vii) Number of subcortical brain infarcts per person as well as the number of these events overall viii) Number of cortical brain infarcts per person as well as the number of these events overall
2. Clinical i) Vascular events a) Number of ischemic stroke or transient ischemic attacks per person as well as the number of these events overall b) Number of occlusive arterial events at other sites, including systemic embolism per person, as well as the number of these events overall c) Number of cerebral venous thrombosis per person as well as the number of these events overall d) Number of venous thromboemboli at other sites per person as well as the number of these events overall e) Number of microvascular thrombosis per person as well as the number of these events overall f) Number of superficial venous thrombosis per person as well as the number of these events overall ii) Death iii) Composite clinical outcomes a) The number of the composite of all thrombotic events: arterial, venous, microvascular, and death per person, as well as the number of these events overall b) The number of Major Adverse Cardiac and Cerebrovascular events per person, as well as the number of these events overall iv) Rate of change in cognitive function assessed by the Montreal Cognitive Assessment in conjunction with the Queen Square Cognitive Assessment score
B. Safety
1. Bleeding: The number of all bleeding events: major, clinically relevant nonmajor, minor per person, as well as the number of these events overall 2. The Number of serious adverse events other than major bleeding per person as well as the number of these events overall 3. The number of cerebral microbleeds assessed with susceptibility-weighted imaging as a surrogate marker of bleeding risk per person as well as the number of these events overall
C. Health economics
1. Quality of life assessed using 5-level EQ-5D-5L 2. Health and social care resource use assessed using trial follow-up visit case report forms 3. Mean incremental cost per quality-adjusted life year
D. Anticoagulation intensity
1. Rivaroxaban i) Rivaroxaban concentration measured with an amidolytic anti-Xa assay
2. Warfarin i) Time in target INR therapeutic range ii) Factor X level measured with an amidolytic factor X assay (LA independent assessment of warfarin anticoagulant effect)
E. Exploratory outcomes
1. Rivaroxaban pharmacokinetic modeling 2. Cerebral blood flow derived from MR perfusion imaging using an arterial spin labeling technique

INR, international normalized ratio; LA, lupus anticoagulant; MR, magnetic resonance.

RISAPS uses a single scanning site for baseline and outcome MRI brain scans in all trial participants so as to optimize reproducibility and minimize variability in assessment of neuroradiological biomarkers.

To ascertain whether APS patients have a different PK rivaroxaban profile compared with other populations where rivaroxaban is prescribed, we will develop a population PK model for rivaroxaban as part of the RISAPS trial.

### Participant timeline

2.6

Potential participants were identified at approved hospital trial sites. Written informed consent was required prior to any trial-specific screening procedures. An overview of the trial schedule (including enrolment, interventions, assessments, and visits) is shown in the Figure. Further details of data collection across the trial can be found in Supplementary File.

**Figure fig1:**
[figure not shown]
Overview of the trial schedule. APS, antiphospholipid syndrome; FBC, full blood count; INR, international normalized ratio; MARS, Medication Adherence Rating Scale; MRI, magnetic resonance imaging; QoL, quality of life; SLE, systemic lupus erythematosus.

### Sample size

2.7

The study sample size target was a minimum of 40 participants. RISAPS is a noninferiority trial. Previous research has suggested that noninferiority margin should be half the SD of the primary outcome from historical studies. Accordingly, sample size calculations are based on a study by Benjamin et al. [29]. This used data from the prospective St George’s Cognition and Neuroimaging in Stroke study of patients with symptomatic lacunar stroke and confluent leukoaraiosis (*n* = 121) to determine sensitivity of MRI to change in small vessel disease (SVD) and calculate sample size estimates for a clinical trial. The mean slope (ie, annual rate of change of WMH volume expressed as a percentage of brain volume) was an increase of 0.8% (95% credible interval, 0.67%-0.95%), with a SD of 0.5. To perform a sample size calculation for RISAPS, we have therefore chosen a noninferiority limit of 0.25, ie, the smallest difference in mean slopes between the two groups that would lead us to conclude inferiority. Our noninferiority limit corresponds to half the between-patient variability in slopes. With the planned sample size of 40, we would be able to establish noninferiority based on approximately 50% of this change (a mean increase of 0.4% per year). We have applied a more liberal type I error rate (alpha, falsely declaring a difference when one does not exist) of 10%, which is in line with most phase IIb trials, given that they are not confirmatory in nature.

In practice, 95% CI for WMH volume change will be ±0.32, given the expected SD of 0.5, due to the use of fully observed data as opposed to the formal sample calculation, which adjusted for power of 80%.

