### Statistical methods for analyzing primary and secondary outcomes

2.11

The primary outcome will be analyzed using a linear mixed effects model to compare the mean rate of change in WMH volume over time between the two randomized groups. This will allow estimation of average slope in each group with respective 95% CIs, while allowing for variability between individuals within each group. Interparticipant clustering will be modeled by fitting a random intercept model, and measurement of differences in rates of WMH volume changes for each participant will be facilitated by introducing a random slope. The primary model will not include explanatory variables apart from the minimization variable. The fixed effects will include randomized groups only. We will restrict the sample to those who have completed the study and provided data for two MRI scans, as we do not feel that the assumptions of Missing At Random (MAR) or Missing Completely At Random (MCAR) are appropriate in this clinical context.

Further details are provided in the Supplementary File, including (i) methods for additional analyses (eg, subgroup and adjusted analyses) and (ii) definition of analysis population relating to protocol nonadherence and statistical methods to handle missing data.

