The follow-up duration of 2 years adopted in RISAPS is based on available data regarding the sensitivity of MRI to the accrual of ischemic brain changes over time. In the prospective St George’s Cognition and Neuroimaging in Stroke study [41], described earlier, changes were detected in multiple MRI markers across 3 years’ follow-up—including WMH volume, but not in cognitive measures. Two years is regarded as an adequate follow-up period to enable meaningful assessment of MRI brain changes, from which a low rate of ischemic progression, alongside favorable secondary clinical outcomes, would support noninferior efficacy of rivaroxaban.

The PK model developed in this trial will be informative for the index population and will also be applicable to other settings where this dose of rivaroxaban might be considered [37].

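### The planning SD of 0.5 is not reconciled with the interval printed beside it, and ±0.32 and 80% power hold only if all 40 participants are analysed

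*Protocol article*

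**What the plan says.** All planning figures are in the Sample size section (2.7) of the protocol article. "The study sample size target was a minimum of 40 participants", and under Interventions (2.4) "Participants were randomized in a 1:1 ratio". The variance input comes from a published cohort of patients with "symptomatic lacunar stroke and confluent leukoaraiosis (*n* = 121"), whose mean annual slope in WMH volume "was an increase of 0.8% (95% credible interval, 0.67%-0.95%), with a SD of 0.5". The noninferiority limit is 0.25, half of 0.5, and the text explains: "Our noninferiority limit corresponds to half the between-patient variability in slopes". With 40 participants the section says that noninferiority could be established for a difference of about 0.4 per year, using 10% alpha and 80% power. It then states that the 95% CI in practice will be ±0.32, given SD 0.5 and fully observed data.

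The Statistical methods section (2.11) defines who enters the primary analysis: "We will restrict the sample to those who have completed the study and provided data for two MRI scans". The article gives no attrition figure.

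**The concern.** Two inputs to the stated precision are doubtful, and both err on the favourable side.

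First, the mean, interval, SD and cohort size stand almost side by side, but the interval is wider than SD 0.5 and 121 patients would produce. Either fewer patients contributed, or the interval contains variation that 0.5 does not. In the second case the missing part is likely to be measurement error, which RISAPS will also have, because each participant's change is the difference between two scans.

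Second, the CI width and the power count 40 analysed participants, while the analysis rule removes anyone without both scans.

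The width of the interval decides what a trial of this size can say about the 0.25 limit. Readers who take ±0.32 and 80% as expected values will overrate what the trial can show.

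**Working it through.** **Inputs.** From Sample size: 40 participants, mean slope 0.8, interval 0.67 to 0.95, SD 0.5, cohort n = 121, limit 0.25, difference 0.4, alpha 10%, power 80%. From Interventions: 1:1 allocation, so 20 per arm. Attrition of 10% or 20% (36 or 32 completers) is an assumption made here.

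**Step 1: reproduce the plan's figures.**
- CI half-width = t(0.975, 38) × SD × √(2/n) = 2.024 × 0.5 × √(2/20) = 0.320. This matches ±0.32, with 20 + 20 analysed.
- Per-arm size = 2 × (1.645 + 0.842)² × 0.5² / 0.4² = 19.3, rounded up to 20, so 40 in total. This matches with 10% alpha taken as two-sided (one-sided 5%), a difference of 0.4 and no dropout. Reading 10% as one-sided gives 30 in total.
- Power at 0.4 from the noncentral t distribution with 20 per arm is 80%.

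**Step 2: compare SD 0.5 with the interval.** Treat the interval as that of a simple mean.
- Printed half-width = (0.95 − 0.67)/2 = 0.14, so SE = 0.14/1.96 = 0.0714.
- SD 0.5 with n = 121 would give 1.96 × 0.5/√121 = 0.089.
- Implied SD = 0.0714 × √n: 0.79 at n = 121, 0.71 at 100, 0.64 at 80. The interval is slightly asymmetric; its two half-widths (0.13 and 0.15) give 0.73 and 0.84 at n = 121.
- n at which SD 0.5 fits = (0.5/0.0714)² = 49.
- If 0.5 is only the between-patient part and all 121 count, the remaining part is √(0.786² − 0.5²) = 0.61.

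**Step 3: recompute precision and power.** Half-widths are t-based. Power is for a difference of 0.4 at one-sided 5%.

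| SD | Completers | 95% half-width | Power at 0.4 |
|---|---|---|---|
| 0.5 | 40 | ±0.32 | 80% |
| 0.5 | 36 | ±0.34 | 76% |
| 0.5 | 32 | ±0.36 | 71% |
| 0.64 | 40 | ±0.41 | 62% |
| 0.71 | 40 | ±0.45 | 54% |
| 0.79 | 40 | ±0.50 | 47% |
| 0.79 | 32 | about ±0.57 | 41% |

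**Step 4: power at the declared limit.** With SD 0.5, 40 completers and one-sided 5%, power at 0.25 is 46%. The stated 80% belongs to 0.4.

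**The case against.** The strongest reply is that no contradiction has been shown. The 0.79 rests on two things the article does not state: that all 121 patients contributed a slope, and that the credible interval behaves like that of a simple mean. An interval from a slope model can also carry residual error and incomplete follow-up, so a between-patient SD of 0.5 plus a residual part of 0.61 fits it. This stands: a reader might infer that 0.5 is wrong and 0.79 right, and the documents do not support that. The reply has a cost, however. If 0.5 excludes measurement error, it is too small as the SD of a two-scan change. The article is ambiguous here, since it also describes the margin rule as half the SD of the primary outcome in historical studies, which reads as an observed SD. On that reading 0.5 is adequate only if about 49 patients effectively contributed.

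Measurement error in RISAPS could differ in either direction. The single scanning site should reduce it. The source cohort, on the other hand, was followed for longer ("changes were detected in multiple MRI markers across 3 years" of follow-up), and a shorter gap between scans gives scan error more weight per year. Neither effect can be sized from the article.

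On retention, 40 is a minimum, the loss rates are assumed, and at SD 0.5 the effect is modest. All of this is true, but the stated figures are computed at exactly 40 analysed, with no allowance given.

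A reader might also infer that only clear superiority could exclude 0.25. That does not follow. With positive differences favouring warfarin, a half-width of 0.50 needs an estimate below 0.25 − 0.50 = −0.25 to exclude the limit, against below −0.50 for superiority. A favourable estimate is needed, not demonstrated superiority.

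**Conclusion.** The point holds as a lack of reconciliation and a best-case presentation, not as a proven error in the SD. The attrition part is firm: the two planning figures reproduce only with 20 + 20 analysed, and the analysis rule does not secure that. Its size depends on the loss rate, which the documents do not give.

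The SD part is conditional. SD 0.5 is adequate only if it is a total SD from about 49 effective patients; otherwise the planning SD should be larger. The range up to about 0.8 is a sensitivity range, with 0.79 near its upper end and not the correct value. It has the larger effect: with every participant retained, power at 0.4 could be as low as 47%. Even on the plan's own SD and full retention, power at the declared 0.25 limit is 46%.

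**What to change.** In the Sample size section:
- State what 0.5 measures (between-patient slopes only, or observed change including scan error) and how many of the cohort contributed to it.
- Label ±0.32 and 80% as the best case: SD 0.5, 40 completers, difference 0.4, one-sided 5%.
- Add a sensitivity range, marked as assumption, over SD 0.5 to about 0.8 and 40 to 32 completers. The table above can serve.
- Give power at the declared limit of 0.25 next to the power at 0.4.

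Before unblinding, compute the pooled SD of observed annualised WMH change blind to arm, and report the CI width that the trial can attain.

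The cost is a few lines of text and one blinded calculation, with no change to treatment, visits or the primary outcome. The downside is that the stated precision and power become less favourable.

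### The sample size section declares a noninferiority limit of 0.25 but ties the 40 participants to 0.4, and 40 gives only about 46% to 61% power against 0.25

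*Protocol article*

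**What the plan says.** All the relevant statements are in the protocol article, section 2.7 (Sample size), unless noted.

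- **Design and size.** "RISAPS is a noninferiority trial", and "The study sample size target was a minimum of 40 participants". Section 2.4 (Interventions) gives 1:1 allocation, so 20 per arm at the minimum.
- **Historical data.** The mean annual slope of WMH volume, as a percentage of brain volume, "was an increase of 0.8% (95% credible interval, 0.67%-0.95%), with a SD of 0.5".
- **Declared limit.** The section says "we have therefore chosen a noninferiority limit of 0.25, ie, the smallest difference in mean slopes between the two groups" that would lead to a conclusion of inferiority. It justifies 0.25 as half the between-patient SD and introduces it for the purpose of the sample size calculation.
- **Value tied to 40.** It continues: "With the planned sample size of 40, we would be able to establish noninferiority based on approximately 50% of this change", given as 0.4% per year, half of the 0.8 mean slope.
- **Error rates.** Alpha is 10%, with no statement of whether this is one-sided or two-sided. The last paragraph refers to "the formal sample calculation, which adjusted for power of 80" per cent.
- **Precision.** The same paragraph expects a 95% interval of ±0.32 at an SD of 0.5.

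The section does not say that 0.4 replaces 0.25, and it gives no power for 40 participants against 0.25.

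**The concern.** A noninferiority trial needs one limit, because that limit is the decision rule. Here one paragraph calls 0.25 the limit and then describes what 40 participants can establish in terms of 0.4. If the upper confidence limit for the difference in slopes (rivaroxaban minus warfarin) falls between 0.25 and 0.40, the first sentence says noninferiority was not shown and the second suggests that it was.

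The clinical meaning differs too. Relative to the reference slope of 0.8% per year, 0.25 tolerates growth about 31% faster (0.25/0.8) and 0.4 tolerates growth 50% faster (0.4/0.8). In SD units they are 0.5 and 0.8, and the section's only rationale, half an SD, supports the first alone.

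The power is also at stake. Because 0.25 is introduced as the basis of the calculation, a reader can easily take the 80% to refer to it.

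**Working it through.** **Inputs.** SD of slopes 0.5, limits 0.25 and 0.4, alpha 10%, power 80% and N = 40 come from section 2.7; 1:1 allocation comes from section 2.4. Assumptions of this check: true difference 0, all 40 analysed, and both readings of the 10% alpha (two-sided, hence one-sided 5%; or one-sided 10%).

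**Step 1: reproduce the 40.** The number per arm is n = 2(z_α + z_β)²(SD/limit)², with z_β = 0.842.

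- Limit 0.40, one-sided 5%: 2 × (1.645 + 0.842)² × (0.5/0.40)² = 2 × 6.18 × 1.5625 = 19.3, so 20 per arm, **N = 40**. This matches the article.
- Limit 0.40, one-sided 10%: 2 × (1.282 + 0.842)² × 1.5625 = 2 × 4.51 × 1.5625 = 14.1, so 15 per arm, N = 30.

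**Step 2: the same formula with the declared limit.**

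- Limit 0.25, one-sided 5%: 2 × 6.18 × (0.5/0.25)² = 2 × 6.18 × 4 = 49.5, so 50 per arm, **N = 100**.
- Limit 0.25, one-sided 10%: 2 × 4.51 × 4 = 36.1, so 37 per arm, **N = 74**.

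**Step 3: power with 20 per arm.** SE = 0.5 × √(2/20) = 0.158. Power is about Φ(limit/SE − z_α); the exact figures use the noncentral t with 38 df.

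| Limit | One-sided alpha | limit/SE | Power, normal | Power, t |
|---|---|---|---|---|
| 0.25 | 5% | 1.58 | 47% | 46% |
| 0.25 | 10% | 1.58 | 62% | 61% |
| 0.40 | 5% | 2.53 | 81% | 80% |
| 0.40 | 10% | 2.53 | 89% | 89% |

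**Step 4: limit for which 40 participants give 80% power.** (z_α + z_β) × SE = 2.486 × 0.158 = 0.39 at one-sided 5%, and 2.123 × 0.158 = 0.34 at one-sided 10%.

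**Step 5: the article's precision figure.** The 95% half-width for the difference between arms is t(0.975; 38 df) × 0.158 = 0.320, which reproduces the ±0.32. The 90% half-width is 0.27. Both exceed 0.25, so with an observed difference of exactly zero neither interval excludes the declared limit. Only an 80% interval (one-sided 10%), with half-width about 0.20, would.

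**Step 6: incomplete follow-up.** Section 2.11 restricts the primary analysis to participants with two scans, and the article gives no loss rate. Over an assumed range of 0 to 20% without a second scan, power against 0.25 (normal approximation) falls from 47% to 41% at one-sided 5%, and from 62% to 55% at one-sided 10%.

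**The case against.** The strongest defence is that the article is open about what 40 participants can do. Only 0.25 is called a noninferiority limit, and it is given an operational definition. The 0.4 is worded as a mean increase. One fair reading is therefore a decision limit of 0.25 with an admission that the reduced sample supports only 0.4. The trial is phase IIb and described as not confirmatory, 40 is a minimum, and the ±0.32 interval is disclosed.

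Part of this stands. Low power can be accepted in a proof-of-principle trial, and the power figures apply at the minimum of 40. That 0.4 acted as the margin is inferred from the exact match with N = 40. But the article says that noninferiority can be established on the basis of 0.4, which cannot be squared with a limit of 0.25. If 0.4 was not the margin, the 80% has no support, because 0.25 does not give 40 under either reading of alpha.

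Four stronger readings are tempting but not supported:

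- **The article claims 80% power against 0.25.** No sentence says so. The 80% appears only where the formal calculation is contrasted with the ±0.32 interval.
- **Only 0.4 can produce 40 participants.** This holds among the two stated values. At one-sided 10%, a limit of about 0.34 fits as well.
- **0.25 was left over from the larger design.** Section 2.1 reports the "revision of sample size target from 140 to 40 participants (minimum" and attributes it to recruitment difficulties. It gives no alpha, power or loss rate for the 140, so the origin of 0.25 cannot be reconstructed.
- **The limit will be picked after the data are seen.** This cannot be established. The analysis plan is not shown and may fix the rule, and section 2.9 says that imaging outcomes are analysed blind.

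**Conclusion.** The inconsistency holds. Section 2.7 contains two incompatible values for the noninferiority criterion, and the 40 participants match the one that the section neither names as its limit nor justifies. Against the declared 0.25, power is about 46% (one-sided 5%) or 61% (one-sided 10%), with 80% requiring about 100 or 74 analysed participants. Leaving the sidedness of the 10% alpha unstated does not rescue 0.25, since both readings fall well short.

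These figures rest on SD 0.5, 20 analysed per arm and a true difference of zero. A true advantage for rivaroxaban would raise power: at one-sided 5%, 80% would need an advantage of about 0.39 − 0.25 = 0.14 per year, which the article does not assume. More than 40 participants would also raise it; missing second scans would lower it.

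**What to change.** Before the unblinded primary analysis, state in the protocol and the analysis plan one limit, and one alpha with its sidedness, that decide the primary conclusion.

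- **If 0.25 is kept**, which is the only value the section justifies, replace the power statement with:

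> With 40 participants and SD 0.5, power against 0.25 is about 46% (one-sided 5%) or 61% (one-sided 10%); 80% power is available only against a limit of about 0.40 (one-sided 5%) or 0.34 (one-sided 10%).

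 Once the sidedness is fixed, only the matching figures need remain.
- **If 0.4 is meant**, say so, delete 0.25, withdraw the half-SD rationale (0.4/0.5 = 0.8 SD) and justify 0.4 separately, including why growth up to 50% above the 0.8 reference would be acceptable.

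The change is to wording and needs no extra patients. The first option costs a less favourable power statement; the second costs the present rationale and requires a new one.
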